## Abstract

**Abstract:**

The SARS-CoV-2 enters into the human body mainly through the nasal epithelial cells. Prevention of SARS-CoV-2 infection at the point of nasal entry is a novel strategy that has the potential to help contain the ongoing pandemic. BioBlock is a nasal spray of anti-SARS-CoV-2 preparation based on virus-neutralising antibodies prepared from colostrum from cows immunised with SARS-CoV-2 spike protein.

This triple-blind placebo-controlled cluster randomised parallel trial seeks to evaluate the efficacy of a BioBlock spray in the prevention and treatment of SARS-CoV-2 infection. Laboratory-confirmed COVID-19 cases and their household members will be randomly allocated to each of either the intervention (BioBlock nasal spray) or the placebo (nasal spray) arms. The intervention is a 14-day course of nasal spray used by index case and household contacts.

In most countries, those with confirmed or suspected infections are requisitioned to isolate at home, putting other members of their household at risk of infection. Therefore, in parallel to the need of household transmission prevention measures, households also present as a good model for infection transmission studies, allowing for the testing of several close contact transmission prevention study hypotheses. Our hope is that if the trial results are encouraging, this will provide new and additional COVID-19 prevention strategies.

**Trial registration:**

ISRCTN48554326 Registered on June 14, 2021

## Administrative information

Note: the numbers in curly brackets in this protocol refer to SPIRIT checklist item numbers. The order of the items has been modified to group similar items (see http://www.equator-network.org/reporting-guidelines/spirit-2727-statement-defining-standard-protocol-items-for-clinical-trials/).

## Introduction

### Background and rationale {6a}

On 11 March 2020, the World Health Organization (WHO) characterised COVID-19 — a condition caused by the severe acute respiratory syndrome coronavirus 2 (SARS-CoV-2) — as a pandemic. By the mid of 2021, the world is approaching the milestone of four million COVID-19 deaths [1].

Control measures (non-pharmaceutical interventions, including business and school closures, restrictions on movement, total lockdowns, social distancing) have been widely implemented to contain the spread of SARS-CoV-2 and have been effective in curbing the COVID-19 epidemic but do not represent desirable nor sufficient long-term strategies. Multiple vaccines are already at our disposal, but these vaccines will not be sufficient to immunise the majority of the seven billion people on the planet (the volumes needed, costs, cold chain requirements and suboptimal acceptance consist just some of the barriers) [2, 3].

The nose is both a source of pathogens and a critical port of entry for infectious agents such as viruses and bacteria. The SARS-CoV-2 enters into the human body mainly through the nasal epithelial cells [4]. In terms of the current pandemic, some evidence indicates that viral titres of SARS-CoV-2 are extremely high in the nose and throat [5]. The human angiotensin I-converting enzyme 2 (hACE2) receptor, used by SARS-CoV-2 to establish infection, is found to be highly expressed in the mucosa of the oral cavity and nasal tissues [6]. A recent review of nasal sprays and gargles with antiviral properties suggests that a number of commonly used antiseptics might mitigate both the progression and transmission of SARS-CoV-2 [7]. Furthermore, there is evidence from animal experiments that engineered human antibody that recognises SARS-CoV-2 S1 spike administered into mouse nostrils blocks infection in mice that were exposed to high titre SARS-CoV-2 pseudovirus 10 h after the initial antibody treatment. The same experiment indicated that the protection against SARS-CoV-2 infection was effective in both nasal and lung areas 7 days after viral exposure [8]. Other SARS-CoV-2 antibody-based protective nasal sprays are in development. At Stanford University, intranasal administration of antibodies harvested from egg yolks of chickens immunised with spike protein of SARS-CoV-2 is tested for the safety and duration of persistence in the nose [9]. Also, it is a viable research question as to whether the regulation of the systemic inflammatory network against the virus can be modulated, starting from the initial phases of the nasal and nasopharyngeal response [4]. Past studies have shown that airway deliveries of various neutralising anti-influenza monoclonal antibodies (bNAbs) were 10- to 50-fold more effective than systemic deliveries of the same bNAbs in treating H1N1, H3N2 and B/Victoria- and B/Yamagata-lineage influenza viral infections in mouse models [10]. Also, in mice, a single intranasal dose of engineered COVID-19 immunoglobulin M (IgM)-neutralising antibody conferred therapeutic efficacy against SARS-CoV-2 [11].

Since the nose is exposed to different concentrations of environmental agents, it is likely that variable nasal infectivity might influence host immune response and, in turn, the variability of the clinical syndrome of COVID-19 [4]. Prevention of SARS-CoV-2 infection at the point of nasal entry is a novel strategy that has the potential to help contain the ongoing pandemic. Exploring whether directly deploying SARS-CoV-2 antibodies into the upper respiratory airway as a prevention or treatment strategy in an exposed household setting is an obvious research need.

### BioBlock — product development background information

SARS-CoV-2-specific neutralising antibodies can be induced in the blood of cattle by immunisation of pregnant cows with specific viral proteins and the specific antibodies are then excreted to colostrum just before calving. For product development, pregnant cows were immunised three times during the third trimester of pregnancy using SARS-CoV-2 S1 receptor-binding domain (RBD) protein, followed by one boost with SARS-CoV-2 trimeric S protein. The immunoglobulins were purified from colostrum, fat and casein were removed and a safe (pasteurised and filtered) colostrum product was prepared from the protein-rich whey. The ability of the resulting formulation to prevent SARS-CoV-2 virus infection and exhibit antiviral properties has been demonstrated using various in vitro assays, which demonstrated blocking of the interaction between the trimeric S protein and hACE2 [12].

The formulation of purified immunoglobulins was prepared into a nasal spray. A clinical trial to assess the durability of the immunoglobulin nasal spray on nasal mucosal surfaces was conducted on healthy volunteers, which confirmed that the formulation persists on the nasal mucosa for at least 4 h [12, 13].

### Objectives {7}

In attempting to determine the effect of intranasal use of SARS-CoV-2 antiviral antibodies, we planned the BioBlock trial to evaluate the efficacy of a spray in the prevention and treatment of SARS-CoV-2 infection.
The main hypothesis of this trial is that using the BioBlock nasal spray by the SARS-CoV-2 carrier and his/her close contacts would be associated with a lower SARS-CoV-2 infection rate in close contact with the SARS-CoV-2 carrier.The secondary hypothesis is that in patients with confirmed SARS-CoV-2 infection, using the BioBlock nasal spray would be associated with improved clinical outcomes.

### Trial design {8}

This is a triple-blind placebo-controlled cluster randomised parallel trial. Clusters, consisting of laboratory-confirmed COVID-19 (index) cases and their household members, will be randomly allocated to each of either the intervention (BioBlock nasal spray) or placebo arms.

A minimum of 124 patients with confirmed COVID-19 (index cases) and their household members will be recruited. Clusters, consisting of an index case and their household members, are randomised (1:1 allocation ratio) to receive application of the BioBlock or to receive placebo spray, both to be administered for 14 days. Participants are contacted on a weekly basis. SARS-CoV-2-infected study subjects are followed up for 21 days to assess symptoms and the course of the disease. Their household members will be tested for SARS-CoV-2 at the baseline and 14-day follow-up and will have exposure information and symptoms recorded. The study will run in two general practitioner (GP) clinics in Tallinn, Estonia.

## Methods: participants, interventions and outcomes

### Study setting {9}

The intervention will be implemented at the general practitioner care level. General practitioners at the two clinics will recruit participants and collect baseline and follow-up data.

### Study population and definitions

The population under investigation consists of the confirmed cases of COVID-19 (irrespective of clinical signs and symptoms) and their close contacts (household members).

For the purpose of this investigation, a household is defined as a group of people living in the same residence. Definition of a household includes two or more people living together in (i) a domestic residence (residential institutions, such as boarding schools, dormitories, hostels or prisons will be excluded) or (ii) a dwelling or group of dwellings with a shared kitchen or common opening onto a shared household space.

Detection of SARS-CoV-2 nucleic acid in a nasopharyngeal specimen will be considered as a confirmed case of COVID-19. COVID-19 cases tested positive within the past 5 days will be considered as newly confirmed [14].

### Eligibility criteria {10}

#### Inclusion and exclusion criteria

Newly laboratory-confirmed cases of COVID-19, aged 16 years or older, with at least one additional household member eligible for participation will be recruited. Household members are eligible for recruitment if they are aged 16 years or older.

Individuals excluded include those who do not live in a household; are pregnant; are receiving active cancer or biological treatment or medications administered by inhalation, or via the naso- and oropharyngeal route; and recovered from confirmed COVID-19 and patients with any organ transplant and with asthma or with known allergies to BioBlock components.

### Who will take informed consent? {26a}

Informed consent will be sought from potential participants by trained research coordinators at study sites. For children aged 16 to 18 years, informed consent to participate will also be sought from their parents.

### Additional consent provisions for collection and use of participant data and biological specimens {26b}

As part of the informed consent process, index patient household members are informed that the study protocol includes the collection of respiratory (nasophryngeal) specimen for SARS-CoV-2 testing and long-term storage of material left over from testing. Samples will be stored in a biobank for potential future studies related to respiratory pathogens, including SARS-CoV-2.

## Interventions

### Explanation for the choice of comparators {6b}

The control condition is placebo, which is ethically justified because no nasally applied agent has definitive proof of efficacy in preventing or treating SARS-CoV-2 infection.

The intervention is a 14-day course of nasal spray used by index case and household contacts.

The experimental group will use the BioBlock intranasally administered virus-neutralising bovine colostrum supplement spray. The spray will be administered to the nasal passages every 4 h.

The control group will use a placebo in the form of a similar spray containing spray base only. The placebo spray will be administered to the nasal passages every 4 h.

Each study subject is allocated one vial of the spray (either active drug or placebo) during the course of the trial.

### Criteria for discontinuing or modifying allocated interventions {11b}

There are no protocol-defined criteria for discontinuing or modifying the study interventions, other than the need for hospitalisation or participant request or, in the case of side effects, requiring of investigation (in all such cases, the use of the study spray will be discontinued).

### Strategies to improve adherence to intervention {11c}

Leaflet with instructions on how to use the spray will be delivered to participants together with the study product. Reading the leaflet will be strongly emphasised in the end of study interview(s).

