### Recruitment {15}

Evidence suggests that the most effective method of recruitment by GPs is opportunistic recruitment [20]. GPs are asked to approach all of their consecutive potentially eligible primary care patients (individuals with a positive SARS-CoV-2 RNA test—“index case”) during the episode of care leading to SARC-CoV-2 testing, check for the first set of inclusion and exclusion criteria and, if appropriate, obtain informed consent for study participation. GPs will review study requirements with the index case and potential eligibility of the household member(s) of the index cases and obtain and document consent. Once the index case has consented to the household study, consent procedures will be initiated for the household members of the index. Members of the household of the index may be recruited into the study during the time of initial contact or an agreed upon alternate time within two business days. Study staff will attempt to approach and recruit all members of the household that the index case has shared contact information. If no household members consent to participate in the study, the index participant will still be enrolled and can continue the study activities. If initially uninfected close contacts of index patients contract SARS-CoV-2 infection (that will be detected either at the day 14 visit or due to symptoms at any point of follow-up), s/he will continue the study under the “index case” protocol (use of the allocated spray for 14 days since infection, and follow-up of the course of the disease at days 7, 14 and 21, after infection detection). All follow-up visits (days 7, 14 and 21) will be phone visits.

The setting for this study is a cluster randomised parallel two-arm RCT, with a cluster (the household consisting of the index patient and his/her household contacts) as a randomisation unit. All cluster members (index and his/her close contacts) will follow the same treatment allocation.

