## Data collection and management

### Plans for assessment and collection of outcomes {18a}

Assessments will be completed at baseline, after use of the spray (at day 14) and at day 21 (for index cases and infected household members) on follow-up. Data will be collected from the results of an interview and respiratory specimen testing (Table 1).

All interviews will be administered by telephone. Enrolled index cases and SARS-CoV-2 RNA-positive household contacts will complete four phone interviews, including the enrolment interview (day 1) and follow-up interviews on days 7, 14 and 21 of enrolment. Enrolled SARS-CoV-2 RNA-negative household contacts will complete three phone interviews, including the enrolment interview (day 1) and follow-up phone interviews on days 7 and 14.

Data collection questionnaires are based on the WHO household transmission investigation protocol for coronavirus disease 2019 (COVID-19) [16]. We will seek information on the sociodemographic characteristics of participants/households; dwelling type and size; household structure; comorbidities; smoking history; household, occupational and community-related exposures; and utilisation of individual prevention measures. At follow-up, we will assess intervention adherence and occurrence of potential side effects. A visual analogue scale (VAS) for measuring nasal spray use adherence will be used [21]. All responses will be stored in a secure Web platform.

The assessment will include interviews administered remotely via a video-conferencing application or by telephone and Web-based testing referral.

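### The adherence section appears to place its only active reminder at the final interview, at or after the end of the 14-day spray course, and the wording does not settle the timing

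*Protocol article*

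**What the plan says.** The section on strategies to improve adherence {11c} contains two measures. The first is written material: "Leaflet with instructions on how to use the spray will be delivered to participants together with the study product". The second is the only active one: "Reading the leaflet will be strongly emphasised in the end of study interview(s".

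The section on the choice of comparators {6b} sets the task for participants: "The intervention is a 14-day course of nasal spray used by index case and household contacts", and, for the experimental group, "The spray will be administered to the nasal passages every 4 h". The placebo has the same interval.

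The section on outcome assessment {18a} fixes the interviews. Index cases and RNA-positive contacts have four, "including the enrolment interview (day 1) and follow-up interviews on days 7, 14 and 21 of enrolment". RNA-negative contacts have three, "including the enrolment interview (day 1) and follow-up phone interviews on days 7 and 14". On adherence, that section describes measurement: "At follow-up, we will assess intervention adherence and occurrence of potential side effects", using a visual analogue scale (VAS). Table 1 places it at days 7, 14 and 21.

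Under Recruitment {15}, a contact who becomes infected moves to the index-case schedule: "use of the allocated spray for 14 days since infection, and follow-up of the course of the disease at days 7, 14 and 21, after" detection. Under Outcomes {12}, the primary outcome is infection of a close contact by day 14.

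**The concern.** An adherence measure has to reach people before or while they use the product. The spray is self-administered at a demanding interval, comes by courier, and is followed up by telephone. Scheduled calls are therefore a natural place for staff to reinforce its use. If the one reminder the section describes is given at the last interview, a site that follows the text exactly will urge participants to read the instructions once the course is finished or finishing. The section would then not do what its title promises.

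The primary analysis is by modified intention to treat, so contacts and index cases who spray irregularly or stop early stay in their arm. That pulls the estimated effect towards no difference, and adherence lost during the course cannot be recovered at analysis.

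**Working it through.** No figure in the plan depends on this sentence, so there is none to reproduce. The check sets the interview days against the spray days.

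**Inputs.** Course length is 14 days ({6b}). Interviews are on days 1, 7, 14 and 21, or days 1, 7 and 14 ({18a}). A contact infected later has 14 days of spray from infection and calls at days 7, 14 and 21 after detection ({15}). The primary outcome is assessed by day 14 ({12}).

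**Reading A: the phrase means the end-of-study interview.** Assume for now that spraying starts on day 1.

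| Group | Last interview | Course days left at that point |
|---|---|---|
| Uninfected contacts | day 14 | 14 − 14 = 0 |
| Index cases, contacts positive at baseline | day 21 | 0; course ended 21 − 14 = 7 days earlier |
| Contacts infected during follow-up | day 21 after detection | 0; about 7 days after the 14 days counted from infection |

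**Reading B: the phrase means the close of each study interview.** The emphasis on day 1 precedes the whole course. On day 7, 14 − 7 = 7 days remain. The emphasis is then well timed for everyone.

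**Delivery lag.** The vials are couriered after baseline assessment and randomisation ({16c}), so spraying may start later than day 1. The article gives no lag; call it *d* days (assumed). The course then ends on day 14 + *d*. At the day-14 interview *d* days are left, and the day-21 interview falls 7 − *d* days after the end. With *d* from 0 to 3, an uninfected contact has 0 to 3 of 14 days left on day 14, and an index case is 7 to 4 days past the end on day 21. On the other side, {18a} itself describes the day-14 assessment as coming after spray use. Whatever *d* is, spray used after day 14 cannot change an outcome fixed by day 14. On Reading A the emphasis therefore contributes nothing to the primary-outcome window.

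**Which reading does the text support?** For Reading A: it is the more literal sense of the phrase, and the optional plural fits because the final interview differs by group. For Reading B: {18a} names only enrolment and follow-up interviews and never defines an end-of-study interview, the phrase has no hyphens, and a reminder to read instructions makes sense only before or during use. Neither set of clues is decisive.

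**The case against.** The strongest reply is that the authors probably meant the close of each interview and that the English is merely loose. On that reading the emphasis already falls on days 1 and 7, and there is no design fault. This stands as a real possibility, and it is why the point concerns what the sentence says and not what the investigators intended. It does not remove the need for a change, because a site cannot tell from the text which calls are meant.

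A second reply is that a journal article leaves call scripts to the full protocol or a site manual. That also stands, and the absence of a script is not raised here. The difficulty is that the article does state a time, and on its literal reading the time is wrong for the purpose.

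Three stronger conclusions are tempting, and the document does not support them:

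- **That the whole adherence strategy comes after spraying is over.** The leaflet arrives with the product, before the first dose. A contact found infected at day 14 goes on spraying, and with a delivery lag some courses may still be running on day 14.
- **That staff have no contact with participants during the course.** The day-7 call exists, the trial design section {8} describes weekly contact, and the general practitioner goes over study requirements with the index case at recruitment.
- **That the sentence costs a stated amount of power.** A reader could assume an adherence level, shrink the effect in proportion and recompute power against the planned 50% reduction. Those levels would be invented, and nothing ties them to the timing of a leaflet reminder. Nor does the sample size section {14} say that the 50% assumes perfect use.

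**Conclusion.** The point holds in a limited form. On the literal reading, the only active adherence measure falls on day 14 for uninfected contacts and on day 21 for index cases and infected contacts. That leaves none of the 14-day primary-outcome window, against 7 days left at the existing day-7 call and the whole window at enrolment. On the alternative reading the timing is sound. The article does not settle which applies, and the leaflet itself is delivered in time under both.

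The consequence is one of direction only. Weaker adherence would dilute the modified intention-to-treat effect, but the share of any such loss due to this wording cannot be derived from the document. The day counts assume that spraying starts on day 1; the conclusion for the primary-outcome window does not depend on that. The correction is worth making because following the sentence literally defeats the section's purpose and putting it right is nearly free.

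**What to change.** In {11c}, replace the phrase about the end of study interview(s) with: *at the enrolment interview (day 1) and the day-7 interview*. Then specify:

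- **Day 1.** Staff tell participants to read the leaflet when the product arrives. They cannot go through it together at this call, because it is couriered with the spray after baseline assessment and randomisation.
- **Day 7.** The adherence VAS is recorded first, so that the reminder does not colour the answer. Staff then repeat the instruction, in the same words in both arms.
- **Contacts who move to the index-case follow-up.** They get the same emphasis at the start of that follow-up.

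The cost is one sentence in the protocol and a script line in calls already scheduled. It needs no extra visit or data item and changes nothing about the spray regimen. It can only help participants who have not yet completed their course.
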